#### Concomitant medications/treatments in both groups

##### Sedation

In the 32.5°-33.5° TTM group, all patients receive sedation with midazolam or propofol combined with fentanyl or sufentanil according to the standard sedation protocol in each participating ICU. Doses are adjusted to obtain a Richmond Agitation Sedation Scale score of −5 [52] and are tapered when body temperature is above 36°C during the rewarming phase.

In the 36.5°-37.5° TTM group, all patients receive sedation with midazolam or propofol combined with fentanyl or sufentanil for the first 12 h after randomization. Doses are adjusted to obtain a Richmond Agitation Sedation Scale score of 0. As indicated in the 2010 ILCOR guidelines [10], no data exist to support the use of sedative agents during TTM at 37°C. The use of sedative agents during TTM at 37°C is therefore restricted, to shorten the time to awakening.

##### Shivering and neuromuscular blockade

Persistent shivering is treated according to a previously published three-step protocol [53] that has been adapted since the publication of the Bedside Shivering Assessment Score (BSAS) [54,55]. The goal is to obtain a BSAS ≤1.Step 1, single intravenous bolus of a hypnotic agent and an opioid, in doses equal to the hourly infusion rates of hypnotic and opioid drugs (i.e., 5-mg intravenous midazolam bolus if the continuous midazolam infusion rate was 5 mg/h);Step 2, intravenous bolus of a nondepolarizing neuromuscular blocker (i.e., 10 mg of cisatracurium);and Step 3, continuous infusion of a nondepolarizing neuromuscular blocker (i.e., cisatracurium in an initial dose of 10 mg/h), with a BSAS target of ≤1; during rewarming, the infusion may be stopped when the core body temperature increases above 35°C.

#### Concomitant prevention of systemic secondary brain injury in both groups

##### Arterial hypotension

Hemodynamic evaluations are conducted to allow blood volume optimization. Hypovolemia is managed with crystalloid or colloid infusion, according to standard practice in the participating ICU. Subsequent evaluations are performed as dictated by the course of the hemodynamic parameters. In accordance with guidelines [10], and in the absence of specific randomized studies, a mean arterial pressure of 65 mmHg and, if measured, central venous oxygen saturation (ScvO_2_) ≥70% are considered reasonable targets [11]. The introduction of vasoactive drug treatment is at the discretion of the physicians, who follow international guidelines [10] and local protocols.

##### Hypoxemia

PaO_2_ and pulse oximetry (SpO_2_) are monitored with the goal of maintaining SpO_2_ ≥ 92%, as recommended [10].

##### Hypercapnia and hypocapnia

PaCO_2_ and end-tidal partial CO_2_ pressure are monitored with the goal of maintaining PaCO_2_ between 35 and 40 mmHg after correcting for body temperature [56].

##### Anemia

The goal is to maintain hemoglobin ≥7 g/dL in patients without ischemic heart disease and ≥10 g/dL in those with ischemic heart disease, as recommended [10].

##### Blood sugar control

A protocol for monitoring blood glucose (or capillary blood glucose) is available to the physician in charge of the patient. In accordance with guidelines [10], specific treatment is recommended in patients with blood glucose values outside the 3.33-10 mmoL/L (60–180 mg/dL) range.

#### Withdrawal of life-sustaining treatments in both groups

Each participating ICU uses its own specific protocol to make decisions about withdrawing life-sustaining treatments. Routine evaluation of the neurological prognosis by an out-of-house consultant is not performed. Nevertheless, to ensure that neurological outcome prediction is performed according to the most recent evidence, our protocol includes the following three measures [57].During the trial preparation phase, all investigators received specific instructions that decisions to withdraw life-sustaining treatments must comply with guidelines issued in 2012 by the ethics committee of the French Intensive Care Society (SLRF) [58]. According to these guidelines, multiple criteria should be used to predict the neurological outcome. Taken individually, the following criteria predict an unfavorable outcome of postanoxic coma after cardiac arrest: bilateral absence of the pupillary response to light or corneal reflex on the third day; bilateral absence of a motor response to pain on the third day; persistent generalized myoclonus during the first 24 hours; an EEG showing an isoelectric line or burst-suppression or anoxic status epilepticus during the first week; and bilateral absence of early cortical activity (N20) detected by somatosensory evoked potentials after the third day and after the end of hypothermia. Although wrongly predicting an unfavorable outcome cannot be entirely avoided, the risk of this occurring can be decreased by relying on more than one criterion. Another important point when seeking to improve prediction accuracy is careful and exhaustive collection of the most severe results from evaluations of each criterion [58].During the trial, the investigators receive newsletters that detail any new information on predicting neurological outcomes after cardiac arrest and any new French or international guidelines about patients with coma after cardiac arrest.The eCRF includes a specific section for collecting the following data in patients with a decision to withdraw life-sustaining treatments: clinical, laboratory, and imaging-study findings on the day the decision was taken; details on the decision-making process; and details on implementation of the decision.

### Outcomes

#### Primary outcome measure

Neurological status 90 days after randomization according to the CPC Scale [59-61]. The CPC is assessed during a semi-structured telephone interview [62]. All interviews of study patients are performed by a single psychologist specifically trained for the study and blinded to the treatment group.

#### Secondary outcome measures

ICU mortalityHospital mortalityDay-90 mortalityDay-90 quality of life evaluated using the 36-item Short Form for Health Survey [63,64]Day-90 patient self-sufficiency evaluated using the Activities of Daily Living (ADL) Index [65,66], modified Barthel’s ADL index [67], and two simple standardized questions [68]Day-90 neurocognitive status evaluated using the telephone version of the Mini-Mental State Examination [69]Estimated number of patients with symptoms of posttraumatic stress on day 90 as assessed using the revised Impact of Events Scale (IES) [70].ICU stay lengthDuration of mechanical ventilation, defined as the time from randomization to final successful extubation. Extubation followed by breathing without invasive ventilatory assistance (not including noninvasive ventilation) for 48 h is classified as successful [71].Incidence of severe bleeding defined as red-blood-cell transfusion or surgery for intracranial hemorrhageIncidence of nosocomial infections in the ICUIncidence of aspiration pneumonia in the ICU, with aspiration pneumonia defined as pneumonia diagnosed within 48 h of mechanical ventilation initiationIncidence of ventilator-acquired pneumonia in the ICUIncidence of nosocomial urinary tract infections in the ICUIncidence of intravascular catheter infections in the ICUNeed for vasoactive drug therapy within the first 48 hNeed for renal replacement therapyNumber of episodes of cardiogenic pulmonary edemaNumber of episodes of seizuresNumber of episodes of severe cardiac arrhythmia.

### Participant timeline

Participant timeline is figured on Table 1.

**Table 1 Tab1:** **Participant timeline**

	**Inclusion**	**D0**	**D1**	**D2**	**D3**	**D4**	**Dn**	**D90**
Eligibility: check inclusion and exclusion criteria	X							
Informed consent	X							
Demographic data	X							
Randomization	X							
Patient characteristics and Physical examination	X							
Vital signs	X							
Coronary angiography	X						X	
Mechanical ventilation		X	X	X	X	X	X	
Biology		X	X	X	X	X	X	
Electrocardiogram	X		X	X	X			
Physical examination	X		X	X	X	X	X	
Treatments		X	X	X	X	X	X	
Vital status		X	X	X	X	X	X	X
Telephone interview by psychologist								X

Dn: Each participant is followed until day 7 or ICU discharge, whichever occurs first.

### Sample size

We expect that 14% of patients in the 36.5°-37.5° TTM group will be CPC 1 or 2 on day 90 and that this proportion will increase by 9% with 32.5°-33.5° TTM. With a two-sided Type I error of 5% and 80% power, and given that two interim analyses will be performed, the required number of patients is 292 per group, i.e., 584 patients in all.

### Recruitment

Patient inclusion started in January 2014 in 22 French ICUs. Enrolment is ongoing. As of February 2, 2015, 161 patients had been included.

## Methods: assignment of interventions

### Allocation

Randomization is centralized, web-based, and accessible 24 hours a day. Randomization is balanced (1:1) and stratified by center and cause of cardiac arrest (probable cardiac cause such as cardiac ischemia or probable noncardiac cause).

### Sequence generation

The randomization sequence was generated by a statistician from the INSERM CIC 1415 not involved in patient recruitment. The sequences are implemented in the software used to collect the data (eCRF).

### Blinding

Blinding of healthcare workers, patients (despite the sedation), and families to the type of temperature management is not feasible. However, the primary outcome is assessed by a psychologist blinded to the treatment arm, during a semi-structured telephone interview [62].

## Methods: data collection, management, and analysis

### Data collection and management

The study data are recorded in an electronic web-based case-report form (eCRF) from the medical records of each patient (source data), by trial-site personnel. The data manager, in cooperation with the coordinating investigator, establishes the trial database by exporting data from the eCRF. Any protocol deviations are recorded in either the eCRF or the medical records.

### Statistical methods

#### Statistical analysis

A predefined statistical analysis plan will be followed. The intention-to-treat principle will be applied. The statistical report will incorporate the data recommended by the CONSORT Statement extension for nonpharmacologic treatment interventions [72].

Descriptive statistics will be used to compare the two randomization groups, without statistical testing. The chi-squared test will be performed to compare the primary endpoint in the two groups. Two interim analyses will be conducted, after the inclusion of 200 and 400 patients, respectively. The rule developed by Peto and Haybittle [73] will be applied, with the significance level set at 0.001 for both interim analyses and the significance level associated with the final analysis set at 0.049 to maintain an overall Type I error of 5%.

Secondary endpoints evaluating binary variables (need for renal replacement therapy, acute cardiogenic pulmonary edema, and binary day-90 neurological outcome) will be compared using the chi-squared test. Secondary endpoints evaluating quantitative variables (biological tests, stay lengths, and mechanical ventilation duration) will be compared using the Student t test or Mann–Whitney test.

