## Methods: participants, interventions, and outcomes

### Study setting

The HYPERION trial is taking place in 22 ICUs in 22 hospitals (8 university and 14 general hospitals) in France.

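### The primary chi-squared test is valid and delivers the planned power, but it leaves out the two randomization factors and so gives up a little precision that could be had almost free

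*Protocol article*

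**What the plan says.** Under Allocation: "Randomization is balanced (1:1) and stratified by center and cause of cardiac arrest", where cause means probable cardiac or probable noncardiac. Under Study setting: "The HYPERION trial is taking place in 22 ICUs in 22 hospitals". The design therefore has 22 × 2 = 44 randomization strata.

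Under Statistical analysis the only primary test named is: "The chi-squared test will be performed to compare the primary endpoint in the two groups". The section names no stratified or adjusted analysis, either primary or supportive, and refers to a predefined analysis plan that is not shown. It sets 0.001 at each interim (after 200 and 400 inclusions) and 0.049 at the final analysis.

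Cause of arrest returns only under Subgroup analysis, in a list of prognostic factors. The Background also links cardiac origin to better prognosis. Center plays no part in the described analysis.

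On the endpoint, the Abstract and the Sample size section use CPC 1-2. The Primary outcome measure section names the CPC Scale without the cut. The Statistical analysis section then places the dichotomized result among the secondary endpoints: "and binary day-90 neurological outcome) will be compared using the chi-squared test".

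**The concern.** Stratified randomization balances the arms within each stratum, so differences between strata no longer add to the chance variation of the treatment comparison. The usual chi-squared variance still counts them. If the strata predict outcome, the standard error is a little too large. The true type I error then falls below nominal and some power is lost.

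The sample size is set at 80% power and its paragraph states no reserve, so precision that costs no extra patients is worth taking. The factors are already known for every randomized patient.

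**Working it through.** **1. The plan's own figure.** Inputs from Sample size: "We expect that 14% of patients in the 36.5°-37.5° TTM group will be CPC 1 or 2 on day 90"; "this proportion will increase by 9% with 32.5°-33.5° TTM"; "With a two-sided Type I error of 5% and 80% power". So p₀ = 0.14, p₁ = 0.23 and the mean is 0.185. The unadjusted pooled formula without continuity correction is

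n = [z(α/2)·√(2·p̄(1−p̄)) + z(β)·√(p₀(1−p₀) + p₁(1−p₁))]² / (p₁−p₀)²

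At α = 0.05: [1.960·√0.30155 + 0.8416·√0.2975]² / 0.0081 = (1.0763 + 0.4591)² / 0.0081 ≈ 291.0, which rounds up to 292 per group, an exact match. At α = 0.049 the result is 293. Power with 292 per group is 80.1% at 0.05 and 79.9% at 0.049. The trial was therefore sized for the test that it names.

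**2. Why the loss should be small.** The pooled variance p̄(1−p̄) equals the average within-stratum variance plus the variance of the stratum rates. Take cause alone, with assumed values of 30% cardiac arrests and an odds ratio of 3, at 14% overall. Rates of 9.62% (noncardiac) and 24.2% (cardiac) fit: 0.7 × 0.0962 + 0.3 × 0.242 = 0.140. The between-stratum part is 0.7 × 0.3 × (0.242 − 0.0962)² = 0.0045, against 0.14 × 0.86 = 0.1204 in total, or about 3.7%. Even a strong factor removes little of the variance of a binary outcome.

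**3. Simulation.** 584 patients, 22 centers of equal expected size, two causes, permuted blocks of 4 within each of the 44 strata, a single test at 0.049, and 3,000 runs per scenario. The effect was calibrated to 14% versus 23%. Assumptions not in the documents: 30% cardiac cause, block size, spread of center effects (SD on the logit scale) and the odds ratio for cause.

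| Center SD, cause OR | Power, chi-squared | Power, Mantel-Haenszel by center × cause | Difference (points) | Type I error, chi-squared | Type I error, Mantel-Haenszel |
|---|---|---|---|---|---|
| about 0, 1 | 80.4% | 80.2% | −0.2 | 4.7% | 4.9% |
| 0.3, 1.5 | 80.2% | 80.6% | +0.4 | 5.0% | 4.9% |
| 0.3, 2 | 79.9% | 80.7% | +0.8 | 4.9% | 5.1% |
| 0.5, 2 | 80.7% | 81.5% | +0.8 | 4.7% | 5.0% |
| 0.5, 3 | 80.1% | 81.8% | +1.7 | 4.7% | 4.8% |
| 0.8, 3 | 81.1% | 84.0% | +2.9 | 4.0% | 4.8% |

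Stratifying by cause alone changes power by −0.1 to +0.8 points. The Monte Carlo standard error is about 0.7 points for power and 0.4 for type I error. Both tests were run on the same simulated data, so the differences are more precise than that.

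**4. Sparseness.** At the final analysis 584 / 44 ≈ 13 patients per cell, with 13.3 × 0.185 ≈ 2.5 good outcomes. At the first interim 200 / 44 ≈ 4.5 patients, with 4.5 × 0.185 ≈ 0.8 good outcomes.

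**The case against.** The best defence is that nothing is broken. The test is valid, the sample size was computed for it, and leaving out the strata errs on the safe side. Choosing an unadjusted test is then a decision about efficiency, and supportive adjusted analyses are commonly left to an analysis plan that is not shown. Stratifying has drawbacks too: many of the 44 cells would carry no information at the first interim, and a logistic model targets a conditional odds ratio although the trial is planned on an absolute difference.

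Most of this stands, and it limits the point to a modest improvement. It does not remove it. The article names the primary test outright, so the proposal changes a stated choice and does not fill a gap left to the analysis plan. The drawbacks can be met by the choice of method and by reporting a risk difference.

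A reader might infer two stronger things. The first is that the trial is underpowered because of this test. It is not: 292 per group reproduces for exactly this comparison. The second is that the primary test could be run on all five CPC categories, because the outcome definition omits the cut and the binary version is labelled secondary. The Abstract states the dichotomy and the Sample size section compares two proportions, so that reading fails. The label is a drafting slip, and the test is chi-squared under either label.

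**Conclusion.** The point holds as a small, nearly free improvement and not as an error. The planned test keeps the type I error (4.0% to 5.0% in simulation against a nominal 4.9%) and gives the planned power. Analyzing by the randomization factors would gain about 0 to 2 power points in most scenarios and about 3 in the extreme one. It would also keep the type I error near nominal (4.8% to 5.1%).

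The size depends on assumed prognostic strength. The documents support the direction for cardiac origin but give no magnitude, and they say nothing on how much outcome differs between centers. Adjusting for further baseline factors might add more, but the documents give no basis for a figure.

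**What to change.** Before unblinding:

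- Make the primary comparison of CPC 1-2 with CPC 3-5, at 0.049, account for the randomization factors. Use either a Mantel-Haenszel test stratified by cause and center, or a logistic model with cause as a fixed and center as a random effect. Name one.
- Report a Mantel-Haenszel or standardized risk difference with its confidence interval, so that the estimate stays on the absolute scale used for the sample size.
- Keep the plain chi-squared as a sensitivity analysis.
- Because the cells are sparse, avoid fixed center terms, and pool or drop center at the two interims.
- Treat adjustment for further baseline covariates as optional.
- Correct the wording: state the dichotomy under Primary outcome measure, and remove the binary day-90 neurological outcome from the secondary endpoints under Statistical analysis.

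The cost is a wording change in the protocol and analysis plan. It needs no new data and no more patients. According to the Recruitment section 161 patients had been included by February 2015, so the first interim at 200 inclusions had not then been reached.

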#### Secondary objectives

To determine whether 32.5°-33.5° TTM for 24 h decreases mortality and morbidity (ICU and hospital stay lengths) and to assess the safety of 32.5°-33.5° TTM.

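### Raw comparisons of stay length and ventilation duration give death no role, so a stay cut short by death counts as favourable and ventilation duration is undefined for patients who die intubated

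*Protocol article*

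**What the plan says.** Three places in the protocol article act together.

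- **Secondary objectives.** The aim is to learn whether hypothermia "decreases mortality and morbidity (ICU and hospital stay lengths"). Stay length is the named measure of morbidity, and a decrease is the benefit sought.
- **Secondary outcome measures.** ICU stay length is listed; hospital stay length is not, although the objective names it. Duration of mechanical ventilation is "defined as the time from randomization to final successful extubation", and success requires 48 h without invasive ventilation. No end point is given for a patient who dies on the ventilator.
- **Statistical analysis.** Intention to treat applies, and the quantitative secondary endpoints get a simple two-sample test: "biological tests, stay lengths, and mechanical ventilation duration) will be compared using the Student t test" or Mann–Whitney.

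The expected prognosis is in the Sample size section: "We expect that 14% of patients in the 36.5°-37.5° TTM group will be CPC 1 or 2 on day 90" and "this proportion will increase by 9% with 32.5°-33.5° TTM". The Abstract defines the poor-outcome category as CPC 3, 4 or 5. The protocol states no expected mortality.

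**The concern.** Length of stay has two kinds of ending, discharge alive and death, and they carry opposite meanings. A raw t or Mann–Whitney comparison treats them alike, so a death on day 2 scores better than survival after a 15-day stay. Because the objective reads a shorter stay as a benefit, any mortality effect enters the stay comparison with the wrong sign. Mortality is itself something the trial hopes to reduce, so this is not a remote case.

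Ventilation duration has a further problem. The stated definition gives no value for a patient who dies intubated, while the stated principle requires that patient to be analysed. Either a value must be supplied that the definition does not contain, or the test is restricted to patients selected by an event after randomization. Switching between the t test and Mann–Whitney cures neither problem.

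**Working it through.** **1. The plan's own figures.** Inputs from the Sample size section: 14% vs 14% + 9% = 23%, two-sided 5%, 80% power. With pooled variance and no continuity correction:

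n = [1.960·√(2·0.185·0.815) + 0.842·√(0.14·0.86 + 0.23·0.77)]² / 0.09² = (1.076 + 0.459)² / 0.0081 ≈ 291, rounded up to 292.

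This matches the plan: "the required number of patients is 292 per group, i.e., 584 patients in all". The sample size is not in dispute.

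**2. How many patients are expected to do badly.** CPC 3–5 is expected in 86% of controls (0.86 × 292 ≈ 251) and 77% of the hypothermia arm (0.77 × 292 ≈ 225), so about 476 of 584, or 81.5%. Deaths by day 90 can be at most this share on the design assumptions. The split between death and CPC 3–4 is not given.

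**3. Direction of the bias.** Let m be mortality in an arm, D the mean stay of those who die and S the mean stay of survivors. The arm's mean stay is m·D + (1 − m)·S. If treatment has no effect on stay given vital status,

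hypothermia minus control = (m_control − m_hypothermia) × (S − D).

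Whenever survivors stay longer than those who die, the arm with fewer deaths shows the longer stay.

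**4. Size, under assumptions.** None of the following is in the documents: log-normal stays, median 4 days in deaths (log-SD 0.7) and 12 days in survivors (log-SD 0.6), mortality 71% vs 80%, 292 per arm.

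- D = 4·exp(0.7²/2) = 5.11 days; S = 12·exp(0.6²/2) = 14.37 days.
- Better arm: 0.71·5.11 + 0.29·14.37 = 7.80 days. Worse arm: 0.80·5.11 + 0.20·14.37 = 6.96 days.
- Difference: 0.09 × (14.37 − 5.11) = 0.83 days longer in the better arm. In simulation about 30% of trials are significant at 0.05 by either test.
- If survivors' stay is truly 15% shorter in the better arm: 0.71·5.11 + 0.29·0.85·14.37 = 7.17 days, still longer than 6.96.
- Break-even: survivors' stay must be multiplied by (6.96 − 3.63)/(0.29 × 14.37) = 0.80. A true 20% reduction among survivors would show as no difference in means.
- Opposite direction, mortality 75% vs 83% with equal death timing: the arm with more deaths looks 0.08 × 9.26 = 0.74 days better, significant in about a quarter of trials.

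**5. Sensitivity.**

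| Setting (log-SD 0.8 in the first and third rows) | Better arm's mean stay | Significant |
|---|---|---|
| Medians 3–4 d (deaths) and 10–15 d (survivors); mortality 86/77, 80/71 or 70/61% | 0.7 to 1.4 d longer | 18–30% (Mann–Whitney), 17–32% (t) |
| Medians as in step 4; mortality 50 vs 41% | 10.6 vs 9.8 d | about 30% (Mann–Whitney) |
| Equal mortality, 80% each | no difference | 4–6% |

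The wrong sign does not need a majority to die. It disappears when mortality and its timing are equal, which identifies death as the mechanism.

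**The case against.** **The SAP may settle it.** The article says a predefined analysis plan will be followed, and how deaths enter a duration is a detail such a plan often holds. A Mann–Whitney test is also compatible with worst-rank scoring. This stands in part: one cannot say which patients or values will actually be analysed. But the article itself fixes the objective, the extubation-based definition and the tests on the raw durations. Those are what mislead, so this is more than a missing detail.

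**The documents do not say that most patients will die.** A reader might infer it from the 14% and 23% good-outcome rates. CPC 3–5 includes living patients, and a poor day-90 outcome does not mean death in the ICU or on the ventilator. This stands. The point needs only substantial mortality that may differ between arms.

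**Much larger distortions can be produced.** With mortality 75% vs 83% and median time to death also moved from 4 to 3 days, the arm with more deaths has the shorter stay, significant in over 99% of trials by Mann–Whitney and 91% by t test. A reader might take that as the size of the problem. It is mostly the assumed timing shift: with equal timing, rejection falls to about 26% and 29%, while the shift alone at equal mortality (79%) gives 93% by Mann–Whitney. The protocol prescribes different sedation by arm, and one might infer that this moves the time of death, but no figure in the documents supports a shift.

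**Mortality is reported alongside.** ICU, hospital and day-90 mortality are separate secondary outcomes, and the data the monitoring board is to see do not include stay length. This stands. It limits the harm and keeps the point away from the primary endpoint, the sample size and the stopping rules.

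**Conclusion.** The concern holds for the secondary endpoints of stay length and ventilation duration, and should be fixed. As written, the stay comparison runs against whichever arm has fewer deaths, and ventilation duration cannot be analysed by intention to treat on its own definition.

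On a 9-point mortality difference and the assumed stays, the false lengthening is about 0.7 to 1.4 days, with roughly 17–32% of trials significant. It is enough to hide a 15% true reduction in survivors' stay. The direction follows from the algebra, provided survivors stay longer than those who die. The size rests on assumed stays and mortality, since the protocol gives neither. A claim that the sign will almost always be significantly wrong is not supported.

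**What to change.** - Replace the raw comparisons with ICU-free and ventilator-free days to a fixed day (28 or 90), with death as the worst rank, compared by a rank test. Alternatively, estimate the cumulative incidence of discharge alive and of successful extubation, with death as a competing event.
- Report raw stay and ventilation duration separately in survivors and non-survivors, descriptively and without tests.
- Align the three sections: reword the secondary objective so that a shorter raw stay is no longer read as less morbidity, either list hospital stay among the secondary outcomes or drop it from the objective, and state how death on the ventilator is handled.

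The cost is protocol and SAP wording, settled before unblinded results are seen. Sample size is unchanged. Dates of death, discharge and extubation are needed for the present endpoints anyway. The note to Table 1 ends follow-up (the Dn column) at day 7 or ICU discharge, whichever is first, so check that the eCRF captures these dates beyond day 7. One small downside is that free-days are less intuitive than raw stay. They also combine mortality with duration, so a difference should be read beside the mortality results.
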